#### Health-related quality of life

Health-related quality of life is assessed by the KvL-H (Kwaliteit van Leven bij Hartpatiënten; *quality of life in cardiac*
*patients*) questionnaire, a validated Dutch translation of the MacNew heart disease health-related quality of life questionnaire [33]. The questionnaire provides an overall score as well as scores on physical, emotional and social domain scales.

#### Anxiety and depression

The GAD-7 (Generalized Anxiety Disorder) and PHQ-9 (Patient Health Questionnaire) are recommended by the Dutch Society of Cardiology to screen CR patients for anxiety and depression [23]. The GAD-7 is a validated seven-item anxiety scale for the screening and assessment of generalized anxiety disorder [34]. The PHQ-9 is a 10-item multipurpose questionnaire for the screening and assessment of depression [35].

#### Patient empowerment, patient satisfaction and health literacy

Patient empowerment is assessed by the PAM13 (Patient Activation Measure) questionnaire [36]. This 13-item questionnaire was previously validated in the Dutch language and assesses patients’ skills for self-management of their health or chronic condition [37].

Patient satisfaction will be assessed by a modified version of the Dutch Consumer Quality Index (CQI) for rehabilitation medicine [38]. Health literacy is assessed by the Dutch version of the Set of Brief Screening Questions (SBSQ-D). This questionnaire consists of 3 questions with a 5-point Likert scale [39].

#### Cost-effectiveness

Both a cost-effectiveness analysis using PAL as effect measure and a cost-utility analysis using quality adjusted life years (QALYs) as outcome measure will be performed. The economic evaluation assumes a societal perspective, including both healthcare and non-healthcare related direct and indirect costs [40, 41]. Healthcare related costs include costs that are related to prevention, diagnostics and treatment; e.g. visits to healthcare professionals (outpatient visits, paramedical visits, general practitioner visits), assessment (exercise testing), professional wages, monitoring devices (accelerometer, heart rate monitor), medication and hospitalizations. Non-healthcare related costs include both costs made by the patient associated with the treatment, e.g. travelling costs and costs related to productivity loss due to absenteeism or presenteeism (the costs for productivity loss due to health issues while at work) in paid and unpaid work. Discounting in cost-effectiveness will not be used due to the time frame of the economic evaluation of one year.

Resource use in both treatment groups is prospectively assessed during the clinical study. Prices published in the Dutch Manual for Costing in economic evaluations and market prices are used [42]. Other costs are measured using the modified iMCQ (Medical Consumption Questionnaire) and iPCQ (Productivity Cost Questionnaire) questionnaires [40, 41], which patients fill out at three, six, nine and twelve months. To assess the effects of the delivery of informal care and to include these in the economic evaluation, informal carers of patients fill out the minimum variant of the iVICQ (Valuation of Informal Care Questionnaire) at three, six, nine and twelve months [43]. Either the friction cost method or the human capital approach is applied to determine the costs of absenteeism or inefficiency from paid work [44].

In the cost-effectiveness analysis, PAL is used as effect measure. In the cost-utility analysis, QALYs are measured using the EQ-5D-5L questionnaire at three, six, nine and twelve months [45].

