## Methods

### Study design

This study is designed as a monocentre randomised controlled trial at Máxima Medical Centre Eindhoven/Veldhoven, the Netherlands. Patients from both Máxima Medical Centre and Catharina Hospital Eindhoven are included in the trial. Three hundred patients with CAD entering outpatient CR are randomly allocated to cardiac telerehabilitation with home-based exercise training (intervention group) or centre-based CR (control group). All subjects are requested to provide written informed consent before study entry. Data are collected at baseline and after three, six, nine, and twelve months. The protocol for this study was approved by the Institutional Review Board of Máxima Medical Centre Veldhoven in the Netherlands. The trial is registered at the Netherlands Trial Registry (NTR) with registration number NTR5156. A completed SPIRIT (Additional file 1: Standard Protocol Items: Recommendations for Interventional Trials) diagram can be found in Table 1.

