### Randomisation, blinding and treatment allocation

Patients are randomly allocated to the intervention or control group after baseline measurements by the investigator using a computerised randomisation system in the web-based database software Castor EDC (Castor Electronic Data Capture, Ciwit BV, Amsterdam, The Netherlands), in which block randomisation with variable block size (4, 6 or 8) is applied. Randomisation is stratified for gender and left ventricular ejection fraction (LVEF ≤ 35% or LVEF > 35%) to ensure balance of the treatment arms with respect to the combinations of the prognostic variables. The investigator, supervising healthcare professionals and patients are not blinded for treatment due to the nature of the intervention.

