### Sample size calculation

Adopted from Kraal et. al [24], we calculated sample size for the primary outcome measure –physical activity energy expenditure (PAEE) – assuming PAEE in healthy subjects was 4.0 ± 1.2 MJ/day [25]. If the difference in the primary outcome measure between the intervention and control groups is 10%, 143 subjects need to be included in either group (power = 0.8 and alpha =0.05). Taking into account loss to follow-up, 150 subjects are included in both groups.

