### Outcome measures

The primary outcome measure is physical activity level, assessed at baseline, three months and twelve months. Secondary outcome measures are physical fitness, Body Mass Index (BMI), blood pressure, health related quality of life, anxiety and depression and patient empowerment, assessed at baseline and at three and twelve months. Other secondary outcome measures include patient satisfaction (assessed at twelve months) and cost-effectiveness (assessed at three, six, nine and twelve months). Health literacy is only assessed at baseline. An overview of the study design is provided in Fig. 1.

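### The EQ-5D-5L is scheduled only from three months, so the one-year QALY has no starting utility and its between-arm difference cannot be adjusted for measured baseline utility

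*Protocol article*

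**What the plan says.** Under Cost-effectiveness, the protocol article plans a cost-utility analysis with QALYs as outcome and fixes the measurement times: "In the cost-utility analysis, QALYs are measured using the EQ-5D-5L questionnaire at three, six, nine and twelve months [45". The horizon is one year: "Discounting in cost-effectiveness will not be used due to the time frame of the economic evaluation of one year".

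Outcome measures gives the same four times: "cost-effectiveness (assessed at three, six, nine and twelve months". The same paragraph names baseline for the other repeated patient-reported outcomes: "health related quality of life, anxiety and depression and patient empowerment, assessed at baseline and at three and twelve months".

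A baseline assessment exists and comes before allocation: "Patients are randomly allocated to the intervention or control group after baseline measurements". Study design says in general terms: "Data are collected at baseline and after three, six, nine, and twelve months". No visible text places the EQ-5D-5L at that baseline.

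The quality-of-life instrument that is taken at baseline is the KvL-H. Its output is described as scale scores, with no utility index or mapping: "The questionnaire provides an overall score as well as scores on physical, emotional and social domain scales".

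**The concern.** A one-year QALY is the area under the utility curve from randomisation to twelve months. The iMCQ and iPCQ can start at three months if they look back over the preceding period. Utility is a point measurement and needs a value at time zero. Without one, the first quarter of the horizon has an end point but no start point, and this is the rehabilitation phase itself, in which the two arms train differently.

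Two things are lost. The absolute QALY total in each arm rests on an assumption about the first three months. And baseline utility, usually the most useful covariate for a QALY comparison, is not available to sharpen the between-arm difference. An analysis plan can choose how to handle the gap, but it cannot recover a utility that was never collected.

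The economic evaluation is prominent in this trial: cost-effectiveness is part of the stated hypothesis, and the cost-utility analysis is one of two planned economic analyses.

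**Working it through.** **Inputs from the document.** EQ-5D-5L at 3, 6, 9 and 12 months; one-year horizon; 150 patients per arm; randomisation after baseline measurements.

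**Inputs assumed, because the document gives none.** Utility SD 0.15 to 0.25; rise in utility over the first three months 0.05 to 0.15; regression slope of later utility on baseline utility 0.5 to 0.7; between-arm difference at three months 0.01 to 0.05.

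**The plan's own figures.** The article states no QALY figure to reproduce. Its sample size for energy expenditure ("assuming PAEE in healthy subjects was 4.0 ± 1.2 MJ/day", a 10% difference, that is 0.4 MJ/day) does reproduce: 142 per group by the normal approximation and 142.25, rounded up to 143, by the t-test. It has no bearing on this point beyond supplying the 150 per arm.

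**Step 1: coverage.** Each three-month interval is 0.25 year, and the trapezoid rule gives each end half of it.
- With a baseline value, the weights at 0, 3, 6, 9 and 12 months are 0.125, 0.25, 0.25, 0.25 and 0.125. Sum = 1.00 year.
- On the stated schedule, the weights at 3, 6, 9 and 12 months are 0.125, 0.25, 0.25 and 0.125. Sum = 0.75 year.
- With the three-month value carried back, they are 0.375, 0.25, 0.25 and 0.125. Sum = 1.00 year, but only by assumption.

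**Step 2: QALY level in each arm.** If utility rises by g over the first three months, carry-back overstates an arm's mean QALY by 0.125 × g.
- g = 0.05: 0.006
- g = 0.10: 0.0125
- g = 0.15: 0.019

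**Step 3: expected between-arm difference.** Let D3, D6, D9 and D12 be the between-arm utility differences. Randomisation makes the expected baseline difference zero.
- Trapezoid: 0.25·D3 + 0.25·D6 + 0.25·D9 + 0.125·D12.
- Carry-back: 0.375·D3 + 0.25·D6 + 0.25·D9 + 0.125·D12.
- Carry-back minus trapezoid: 0.125·D3. For D3 of 0.01 to 0.05 this is 0.001 to 0.006 QALY.
- If the difference is a constant d at all four visits, the two give 1.000·d and 0.875·d. The ratio is 1/0.875 = 1.143, an inflation of about 14% whatever the size of d.

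**Step 4: chance imbalance at baseline.** SE = SD × √(2/150).
- SD 0.15: 0.017 (95% range ±0.034)
- SD 0.20: 0.023 (±0.045)
- SD 0.25: 0.029 (±0.057)

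Under carry-back, an imbalance of one SE moves the unadjusted QALY difference by slope × SE: from 0.5 × 0.0173 = 0.009 to 0.7 × 0.0289 = 0.020. This is variation that adjustment for baseline utility would largely remove.

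**The case against.** The strongest answer is that the incremental QALY, which is what a cost-utility ratio needs, can still be estimated. Since the expected baseline difference is zero, the trapezoid expression in Step 3 uses only visits that are measured. This stands, and it rules out three stronger readings that a reader might infer.

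- *That the per-patient error of Step 2 carries into the cost-utility ratio.* It is an error of level in each arm and largely cancels. What remains under carry-back is 0.125·D3, which is much smaller.
- *That chance imbalance in utility biases the result.* An unadjusted randomised comparison already carries that variation in its standard error. The loss is precision.
- *That no adjustment is possible.* KvL-H, PHQ-9 and GAD-7 are all taken at baseline and can serve as proxy covariates. But the adjustment is partial, the visible text does not plan it, and a proxy covariate does not by itself supply a starting utility.

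It can also be said that covariates and the handling of the first interval belong in an analysis plan that is not shown. That is fair for the method. It does not answer a data-collection schedule that is stated twice, consistently, in a paragraph that names baseline wherever it is meant.

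Finally, the SPIRIT diagram (Table 1) and the flowchart (Fig. 1) are not shown and could list a baseline EQ-5D-5L. Their abbreviation lists do not name the instrument, but they also omit the iMCQ, iPCQ and iVICQ, so they do not settle the matter. This limits confidence in the finding.

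**Conclusion.** The point holds as a weakness in a secondary analysis. On the text as written, a quarter of the QALY horizon has no starting utility, and the comparison cannot be adjusted for measured baseline utility, only partly through proxies.

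The consequences are that absolute QALYs depend on an assumption (0.006 to 0.019 per arm under carry-back, for an assumed early rise of 0.05 to 0.15) and that the between-arm difference loses precision (SE of chance imbalance 0.017 to 0.029 for an assumed SD of 0.15 to 0.25). The only systematic effect on the difference arises if the three-month value is carried back: an inflation of 0.125·D3, or about 14% when the difference is constant and the true path over the first three months is linear from equal starts. The article does not say that carry-back will be used.

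The documents do not support a claim that the cost-utility result is invalid or biased by design. The primary outcome and the cost-effectiveness analysis based on physical activity level, which has a baseline value, are untouched. This is a cheap improvement, not a condition for the trial's validity.

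**What to change.** - Add the EQ-5D-5L to the pre-randomisation baseline questionnaires for all patients still to be enrolled, and amend Outcome measures and Cost-effectiveness to say so.
- Compute QALYs by area under the curve from baseline, and estimate the between-arm difference by regression with baseline utility as covariate.
- For patients already enrolled, multiply impute baseline utility from baseline KvL-H, PHQ-9 and GAD-7. KvL-H and EQ-5D-5L are both taken at three and twelve months, so the trial's own data can also inform the imputation model. Do not carry the three-month value back.
- Report a sensitivity analysis in patients with a measured baseline, and note that this subset is defined by calendar time. The article gives recruitment as running from May 2016 to an expected end in September 2017, so the size of the subset depends on when the change is made.
- If Table 1 or Fig. 1 already lists a baseline EQ-5D-5L, the remedy is to correct the two text sections to match.

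The cost is one short extra questionnaire at an existing assessment, a minor amendment and some imputation work.

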### Statistical analysis

All analyses will be performed on an intention-to-treat basis. Descriptive statistics will be used to report demographics and baseline characteristics. Between-group differences and within group differences in the outcome measures will be evaluated using multivariate analysis of variance (MANOVA). Pearson’s correlation coefficient (r) will be applied to quantify relations between changes in variables. For all statistical comparisons, the level of significance will be set at p < 0.05. Analyses will be carried out in the statistical software package SPSS (version 22).

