We hypothesize that cardiac telerehabilitation using modern communication methods and multiple evidence-based behavioural change strategies including relapse prevention, will result in improved self-management skills and sustainable behavioural change. We expect this will translate to a superior increase in physical activity levels when compared to centre-based CR. Therefore, the objective of the SmartCare-CAD trial is to investigate whether cardiac telerehabilitation using modern technology and multiple behavioural change strategies results in better long-term physical activity levels than centre-based CR in patients with CAD. For telerehabilitation, a personalised patient-centred web application is used, comprising remote monitoring of exercise and physical activity behaviour and on-demand video consultation. In addition, both strategies will be compared with respect to physical fitness, modifiable cardiovascular risk factors, quality of life, anxiety and depression disorders, patient empowerment, patient satisfaction and cost effectiveness.

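### The only between-group method named, a MANOVA on the outcome measures, is not the PAEE comparison the trial was sized for and, on either reading, does not isolate the long-term PAEE difference

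*Protocol article*

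**What the plan says.** All references are to the protocol article.

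- **Objective (Background).** The trial asks whether telerehabilitation "results in better long-term physical activity levels than centre-based CR in patients with CAD". The hypothesis is a superior increase in physical activity.
- **Sample size calculation.** PAEE is the only variable, "assuming PAEE in healthy subjects was 4.0 ± 1.2 MJ/day". The text continues: "If the difference in the primary outcome measure between the intervention and control groups is 10%, 143 subjects need to be included in either group", at power 0.8 and alpha 0.05. Adding loss to follow-up gives 150 per group.
- **Outcome measures.** Physical activity level, which the Measurements section says is determined by PAEE, is the single primary outcome, measured at baseline, 3 and 12 months. On the same schedule: "Secondary outcome measures are physical fitness, Body Mass Index (BMI), blood pressure, health related quality of life, anxiety and depression and patient empowerment".
- **Statistical analysis.** "Between-group differences and within group differences in the outcome measures will be evaluated using multivariate analysis of variance (MANOVA". Then: "For all statistical comparisons, the level of significance will be set at p < 0.05". This is the only between-group method named. The section does not separate primary from secondary outcomes and does not say whether the dependent variables are the different outcomes or the repeated visits of one outcome.

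**The concern.** The question and the sample size concern one variable. The named test is multivariate, and its null depends on what is put into it.

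With the outcomes as dependent variables, the null is that the whole vector of means is equal in both arms. The test responds to a difference in any linear combination of fitness, BMI, blood pressure, quality of life, anxiety, depression, empowerment and PAEE, in either direction. This matters in practice because the Background also predicts better self-management skills, which the PAM13 measures. The authors therefore expect at least one outcome other than PAEE to differ.

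A significant result could then reflect empowerment or fitness alone and would not support a claim about physical activity. A non-significant result could not be read at the stated 80% power, because that power belongs to a different test.

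**Working it through.** **Inputs.** From the Sample size calculation: mean 4.0 and SD 1.2 MJ/day, difference 10%, alpha 0.05, n = 143 per group. The standardised effect is d = 0.10 × 4.0 / 1.2 = 0.333. From Outcome measures: seven secondary outcomes share the schedule of the primary, so p = 8, counting blood pressure and quality of life once each. The article gives no correlations, so they are assumed and varied.

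**1. The plan's own figure.** A two-sided two-sample t-test with d = 0.333 and 143 per group has power 0.802 (142 per group gives 0.799). A one-sided normal approximation would need only 112. The 143 is correct, and it belongs to a univariate two-sided test.

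**2. Joint MANOVA, only PAEE differs.** With two groups this is Hotelling's T². Power comes from the non-central F with p and 2n − p − 1 = 277 degrees of freedom and noncentrality λ = (n/2)·D². With a common correlation r, D² = d²/(1 − R²) and R² = (p − 1)r² / [1 + (p − 2)r].

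Example, r = 0.3: R² = 7 × 0.09 / 2.8 = 0.225; D² = 0.1111 / 0.775 = 0.1434; λ = 71.5 × 0.1434 = 10.25; power 0.586.

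| r | 0 | 0.2 | 0.3 | 0.5 | 0.6 | 0.7 |
|---|---|---|---|---|---|---|
| λ | 7.94 | 9.10 | 10.25 | 14.12 | 17.57 | 23.34 |
| power | 46% | 53% | 59% | 76% | 86% | 95% |

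Power reaches 80% only if the other seven outcomes explain about 48% of the variance of PAEE. At r = 0, 80% power would need 275 per group.

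**3. Joint MANOVA, no PAEE effect, one other outcome differs by 0.333 SD.** By symmetry λ is the same, so rejection is 46%, 53% and 59% at r = 0, 0.2 and 0.3. A PAEE test would reject 5% of the time. If three others differ by 0.3 SD, rejection is about 89–90% at r = 0 to 0.3. For one differing outcome, these rejections become more frequent as r rises.

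**4. Repeated-measures MANOVA of PAEE over baseline, 3 and 12 months.** The effect matching a superior increase is group by time: a two-dimensional test on the changes from baseline, with 2 and 283 degrees of freedom. With equal within-patient correlation ρ and a 0.333 SD effect at 12 months only, D² = (2/3)d²/(1 − ρ).

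Example, ρ = 0.4: D² = 0.0741 / 0.6 = 0.1235; λ = 71.5 × 0.1235 = 8.83; power 0.757.

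| ρ | 0.3 | 0.4 | 0.5 | 0.7 |
|---|---|---|---|---|
| power | 69% | 76% | 83% | 97% |

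D² is identical for an effect at both follow-up visits, at 12 months only, or at 3 months only. The test therefore rejects equally often when the effect has gone by 12 months.

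**5. A single 12-month contrast adjusted for baseline PAEE.** The effect becomes d/√(1 − ρ²): 0.349 at ρ = 0.3 and 0.467 at ρ = 0.7. With 143 per group, power is 84% and 98%.

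**The case against.** The strongest reply is that the joint reading is not forced. The sentence assigns MANOVA to within-group as well as between-group differences, and within-group differences need repeated visits. A repeated-measures MANOVA for each outcome fits the wording, mixes no outcomes, and tests physical activity. Patient satisfaction and cost-effectiveness are measured on other schedules, which also makes one omnibus test over everything awkward. This stands: a reader might infer that the article commits to a single test across all outcomes, and it does not say so.

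A reader might also infer that the trial simply lacks 80% power for PAEE. The article does not support that. It gives neither the dependent variables nor any correlation, the joint test passes 80% between r = 0.5 and 0.6, and the group-by-time test exceeds 80% from ρ = 0.5. Nor should the repeated-measures reading be judged by its group main effect, which averages in the pre-randomisation baseline; the hypothesis is about an increase.

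Finally, this is a condensed article, and a fuller protocol or SAP not shown may define the model. Missing model detail is accordingly not the complaint. The complaint is that the one method stated does not correspond to the stated objective and sample size. The reply does not remove that, because neither reading yields the comparison behind the 143.

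**Conclusion.** The point holds in a conditional form. The sample size is right for a univariate PAEE comparison, and the analysis section names a different test.

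- **Outcomes as dependent variables:** the null is wrong for the objective whatever the correlation. The size of the problem (46–59% rejection with no PAEE effect; 46–76% power for PAEE) rests on eight outcomes, 143 per arm, d = 0.333 and the assumed correlations of 0–0.3 and 0–0.5 respectively.
- **Visits as dependent variables:** the test concerns physical activity, and power is short only at within-patient correlations of about 0.3–0.4 (69–76%). It still does not isolate the long-term difference that the objective names.

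Because the sentence admits both readings, it also leaves open which null decides superiority. This should be corrected. It does not show that the trial is too small.

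**What to change.** In Statistical analysis, replace MANOVA as the confirmatory method with one between-group contrast: a linear model for PAEE at 12 months with baseline PAEE as covariate, reported as the mean difference in MJ/day with 95% confidence interval and two-sided p-value. State that superiority in physical activity is concluded from this contrast alone. Analyse each secondary outcome in its own model, labelled secondary. If a MANOVA is kept, label it exploratory.

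The 143 per arm then matches the test used, with some power in reserve from the baseline adjustment.

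The cost is a few sentences before database lock, with no extra patients, visits or data. The small downside is losing one omnibus p-value across outcomes.

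### MANOVA as the only named between-group method discards patients with an incomplete outcome vector, which sits badly with intention-to-treat and the expected loss to follow-up

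*Protocol article*

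**What the plan says.** The Statistical analysis section of the protocol article makes three statements that matter here:

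- Population: "All analyses will be performed on an intention-to-treat basis".
- Method: "Between-group differences and within group differences in the outcome measures will be evaluated using multivariate analysis of variance (MANOVA"). No other method for comparing the arms is named.
- Software: "Analyses will be carried out in the statistical software package SPSS (version 22").

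Under Outcome measures, the primary outcome is measured repeatedly: "The primary outcome measure is physical activity level, assessed at baseline, three months and twelve months". Under Sample size calculation, losses are expected: "Taking into account loss to follow-up, 150 subjects are included in both groups". The article mentions neither imputation nor a model that keeps partly observed patients. It also does not say whether the MANOVA runs over time points, over different outcomes, or both.

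**The concern.** MANOVA, like the repeated-measures GLM through which SPSS fits it, needs a full outcome vector for each patient. By default, SPSS removes a case with any missing element.

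If the vector is PAEE over time, a patient who misses the 3-month recording but has a valid 12-month recording leaves the analysis. That 12-month value is the one that answers the trial's question about long-term activity. If the vector combines several outcomes, one missing outcome has the same effect.

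The set analysed is then those with complete data, not everyone randomised. Two things are at stake: power, because observed values are thrown away, and bias, if patients with complete data differ in activity from those without.

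**Working it through.** **Inputs from the article (Sample size calculation).** Mean and SD: "assuming PAEE in healthy subjects was 4.0 ± 1.2 MJ/day". Target: "If the difference in the primary outcome measure between the intervention and control groups is 10%, 143 subjects need to be included in either group". Error rates: "power = 0.8 and alpha =0.05". The difference is 0.10 × 4.0 = 0.4 MJ/day, and the standardised difference is d = 0.4/1.2 = 0.333. Sidedness is not stated.

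**The plan's own figure.** A two-sided two-sample t-test needs 142.2 per arm, rounded up to 143. This reproduces the plan; a one-sided test gives 112 and does not match. The allowance for loss is 1 − 143/150 = 4.7%.

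**Complete patients.** If a fraction m of values is missing independently at each of 3 and 12 months, the complete fraction is (1 − m)². Setting (1 − m)² = 143/150 gives m = 2.4% per visit, which uses up the whole allowance. The rates below are assumptions, because the article gives none. Power is for a two-sided two-sample t-test of the 12-month values with d = 0.333, without baseline adjustment in any column.

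| Missing per visit | Complete per arm | Power, complete patients only | Power, 12-month values alone | Power, all 3- and 12-month values |
|---|---|---|---|---|
| 0% | 150 | 82.1% | 82.1% | 82.1% |
| 5% | 150 × 0.9025 = 135.4 | 78.0% | 80.1% (142.5 per arm) | 80.5-81.0% |
| 10% | 150 × 0.81 = 121.5 | 73.5% | 77.9% (135 per arm) | 78.8-79.7% |

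The last column assumes a correlation ρ of 0.5 to 0.7 between the 3- and 12-month values. The information per patient, in units of 1/SD², is

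I = p(both) × R⁻¹ + diag(p(3 only), p(12 only)),

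where R is the 2 × 2 correlation matrix. The effective number per arm at 12 months is 150 divided by the 12-month diagonal element of I⁻¹. At 10% missing, p(both) = 0.81 and each single-visit fraction is 0.09.

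- ρ = 0.5: diagonal 0.81/0.75 + 0.09 = 1.17; off-diagonal −0.81 × 0.5/0.75 = −0.54. Element: 1.17/(1.17² − 0.54²) = 1.086. Effective n = 150/1.086 = 138.1; power 78.8%.
- ρ = 0.7: diagonal 0.81/0.51 + 0.09 = 1.678; off-diagonal −0.81 × 0.7/0.51 = −1.112. Element: 1.678/(1.678² − 1.112²) = 1.062. Effective n = 141.3; power 79.7%.

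The part due to dropping incomplete patients is therefore 78.8 − 73.5 = 5.3 to 79.7 − 73.5 = 6.2 points at 10% per visit, or 77.9 − 73.5 = 4.4 points against the 12-month values alone. At 5% per visit it is 2.5 to 3.0 points against the all-values model.

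**Monotone drop-out.** If 10% are lost by 12 months and nobody returns, 150 × 0.90 = 135 per arm are complete, with power 77.9%. A model using all observed values gives 77.9% if everyone leaves before 3 months (no gain) and 78.9-79.9% if everyone leaves after 3 months (1 to 2 points).

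**Bias.** The simulation had 2,000 runs, 150 per arm, SD 1.2 and a true 12-month difference of 0.4 MJ/day. Drop-out of 16-19% before 12 months depended on 3-month activity, with correlations of 0.5 and 0.7. All drop-out settings are assumptions.

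| Who drops out | Completers only (MJ/day) |
|---|---|
| Unrelated to activity | 0.40 |
| Less active patients, equally in both arms | 0.37-0.38 |
| Activity-related in the intervention arm only | 0.51-0.56 |
| Activity-related in the control arm only | 0.19-0.25 |

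A regression estimate using all observed data gave 0.395 to 0.404 in every row.

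**The case against.** The strongest reply is that the article says nothing about excluding patients. Missing-data handling is commonly left to the statistical analysis plan, which is not shown. Imputation before MANOVA would remove the conflict. Intention-to-treat also means analysis by allocated arm, which MANOVA respects. This stands in part: a reader might infer that the section flatly contradicts itself, and the documents support only that the named method, run without imputation, fits intention-to-treat badly. The choice of MANOVA itself is fixed in the text, so this is more than an omitted detail.

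Other stronger readings also go too far:

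- *That MANOVA costs the whole step from 80% to 73% power.* No model recovers missing 12-month values completely, so the fair comparison is with 79-80% under the same missingness.
- *That missing baseline recordings push the loss further* (150 × 0.9³ = 109 per arm, 69% power). Randomisation follows the baseline measurements, so a 10% baseline loss has no basis in the article.
- *That reasons for missing data differ by arm.* The Measurements section shows only that data return differs: intervention patients upload, controls hand the sensors back. Differential missingness is possible, not shown.
- *That the result is valid only if data are missing completely at random.* This is too absolute: with activity-related drop-out equal in both arms, the simulated bias was only 0.02 to 0.03 MJ/day.
- *That MANOVA cannot yield a difference in MJ/day.* SPSS GLM also reports estimates and confidence intervals for each outcome.
- *That within-group tests will support the efficacy claim.* The article does not say so.

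**Conclusion.** The concern holds in a limited form. As written, the analysis discards observed 12-month values from patients who miss another element of the outcome vector, in a trial that claims intention-to-treat, expects losses and has room for only 4.7% incomplete patients. The avoidable power loss is about 4 to 6 points if 10% of values are missing independently at each follow-up visit, about 2 to 3 points at 5%, and between none and about 2 points if 10% drop out monotonically. These figures rest on assumed missingness rates and, for the all-values model, on an assumed correlation of 0.5 to 0.7. If several outcomes share one vector, the loss is larger. Bias becomes serious against a 0.4 MJ/day target only if activity-related missingness differs by arm. The method should be changed, but the documents do not show that the result would be invalid without the change.

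**What to change.** For PAEE, replace MANOVA with a linear mixed model for repeated measures:

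- Use all observed 3- and 12-month values, with arm, visit and arm-by-visit interaction and an unstructured covariance.
- Adjust for baseline PAEE and the stratification factors, gender and LVEF group.
- Take the 12-month difference in MJ/day with its 95% confidence interval as the main result.
- Add one missing-not-at-random sensitivity analysis that includes all randomised patients, for example delta-adjusted multiple imputation. This also covers patients with no follow-up value, whom the mixed model leaves out.
- Treat within-group changes as descriptive.

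SPSS MIXED can fit the model, so the change needs no new patients, data or software. The cost is revised analysis wording and slightly more analysis work.
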